
### Unblinding

2.7

During the intervention phase, participants will undergo systematic evaluation to identify potential complications associated with taVNS and life-threatening symptoms. Potential adverse events may include ear dermatitis, local bleeding at the stimulation site, ear pain, bradycardia, and cardiac arrhythmias. In the event of such complications, the unblinding procedure will be promptly initiated to minimize potential risks related to the intervention.

### Anesthesia

2.8

Patients will undergo routine preoperative education and anesthesia consultation. During this period, we will collect relevant medical history, inform patients about anesthesia details and potential risks, and obtain informed consent for anesthesia and experimental procedures. Upon entering the operating room, peripheral venous access will be established, and monitoring of blood pressure, electrocardiogram, and pulse oxygen saturation will commence. Radial arterial and internal jugular venous catheters will be placed to monitor invasive arterial blood pressure and central venous pressure (maintained at <5 cm H_₂_O during surgery). Anesthesia induction will be achieved through intravenous administration of midazolam (0.05 mg/kg), etomidate (0.3 mg/kg), sufentanil (0.5 μg/kg), and cisatracurium (0.05 mg/kg), followed by rapid sequence intubation. After intubation, mechanical ventilation will be initiated with the following parameters: tidal volume 6–8 mL/kg, respiratory rate 12 breaths/min, inspiration-to-expiration ratio 1:1.5, inspired oxygen concentration 100%, oxygen flow rate 2 L/min, with end-tidal carbon dioxide partial pressure maintained between 35 and 45 mmHg. Anesthesia will be maintained using a combined intravenous and inhalational technique: continuous intravenous infusion of propofol at 4–6 mg/kg/h, remifentanil at 0.1–0.3 μg/kg/min, and 1% sevoflurane to maintain the bispectral index (BIS) between 40 and 60. Cisatracurium 0.05 mg/kg will be administered intermittently as needed. Vasoactive agents may be used to maintain heart rate and blood pressure within normal ranges. Tidal volume and respiratory rate will be adjusted to maintain end-tidal CO_₂_ between 35–45 mmHg. Fluid management will be tailored to intraoperative conditions, with central venous pressure maintained at <5 cm H_₂_O during hepatectomy. Sevoflurane will be discontinued 30 min before surgery’s end, and all anesthetic agents will be immediately stopped upon completion. The patient will be transferred to the post-anesthesia care unit (PACU). Postoperative patient-controlled analgesia (PCA) will contain sufentanil 1.5 μg/kg, tropisetron 6 mg, and normal saline 100 mL, with a continuous infusion rate of 2 mL/h, PCA dose of 0.5 mL, and a lockout interval of 15 min. Upon PACU arrival, atropine 0.5 mg and flumazenil 0.5 mg will be administered. Extubation will occur when the patient responds to verbal stimuli, muscle tone normalizes, and respiratory parameters are optimal. In the PACU, patients with a Numeric Rating Scale (NRS) pain score exceeding 5 may receive rescue analgesia. Patients with a Steward score greater than 4 can be transferred to the ward.

### Study interventions

2.9

On the day before surgery, potential participants will be identified from elective surgical schedules. Active-taVNS or sham taVNS groups will be administered at four specific time points (as shown in Table 1): (1) at the onset of the first hepatic portal occlusion, (2) post-extubation, (3) on postoperative day 1 (6:00–7:00 a.m.), and (4) on postoperative day 2 (6:00–7:00 a.m.). taVNS will be performed using a transcutaneous electrical stimulation device (tVNS501, Reshen, Changzhou, China). Electrical stimulation will be applied via electrodes positioned near the auricular branch of the vagus nerve within the left ear cavity (as shown in Figure 2), a location demonstrated to optimally activate brain regions associated with organ control (30). Given the absence of clinical studies on taVNS’s hepatoprotective effects, stimulation parameters will be based on preclinical research (23). For active stimulation, before entering the operating room, independent researchers not involved in the research will calibrate the equipment, initiating stimulation amplitude at 0 (pulse width: 200 ms; frequency: 20 Hz) and incrementally increasing by 1 based on patient response. When participants report discomfort, display pain-indicative facial expressions, or when stimulation causes oxygen saturation to drop below 95% or heart rate to increase by more than 20%, the amplitude will be reduced to just below the previous threshold and maintained at a constant stimulus intensity output for 60 min. For the sham stimulation group, device placement and parameters remained consistent, with the sole difference being electrical current output (all device screens were adjusted and darkened before entering the room, and no current was applied in the sham group). The collection of the intensity of the first intervention will be conducted on the day before the surgery after the informed consent form is signed by the patient upon enrollment. Throughout the intervention, trained researchers strictly will adhere to the protocol and closely monitored participants’ responses to ensure no adverse reactions. If participants report intolerable discomfort, stimulation will be immediately terminated.

**Table 1 tab1:** The study schedule for enrollment, treatments, outcome measurements, and data collection.

Study period									
Timepoint	Enrollment	Allocation	Post-allocation						
Pre-2	0	Pre-1 (t0)	Pod-0 (t1-t2)	Pod-1 (t3)	Pod-2 (t4)	Pod-3 (t5)	Pod-5 (t6)	Pod-30 (t7)
Enrollment									
Inclusion criteria	☑								
Exclusion criteria	☑								
Informed consent	☑								
Randomization									
Allocation			☑						
Interventions									
Active-taVNS group				☑	☑	☑			
Sham taVNS group				☑	☑	☑			
Outcome measurement									
ALT			☑			☑		☑	
AST			☑			☑		☑	
TBA			☑			☑		☑	
DBIL			☑			☑		☑	
TBIL			☑			☑		☑	
BUN			☑			☑		☑	
Cr			☑			☑		☑	
IL-6			☑			☑			
TNF-α			☑			☑			
FRAIL			☑						
NRS					☑	☑		☑	☑
CAM			☑		☑	☑		☑	☑
SAS			☑		☑	☑		☑	☑
I-FEED					☑	☑	☑	☑	
FSS			☑		☑	☑		☑	☑
QoR-15			☑		☑	☑		☑	☑
Adverse events			☑	☑	☑	☑	☑	☑	☑

According to SPIRIT 2013 statement: defining standard protocol items for clinical trials. Pre, preoperative day; Pod, postoperative day; ALT, Alanine aminotransferase; AST, Aspartate aminotransferase; TBA, Total bile acids; TBIL, Total bilirubin; DBIL, Indirect bilirubin; BUN, Blood Urea nitrogen; Cr, Creatinine; IL-6, Interleukin-6; TNF-α, tumor necrosis factor-α; FRAIL, Fatigue, Resistance, Ambulation, Illness and Loss of Weight Index; NRS, Numerical Rating Scale; CAM, The Confusion Assessment Method; SAS, Simpson-Angus Scale; IEED, Intake, feeling nauseated, emesis, exam and duration of symptoms; FSS, Fatigue Severity Scale; QoR-15, Quality of Recovery-15.

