### Randomization and blinding

2.6

Participants will randomly be allocated to active-taVNS treatment or sham taVNS groups at a 1:1 ratio, based on a computer-generated random number sequence. The allocation process is strictly confidential and managed by administrative personnel uninvolved in study design and implementation. Each participant will be assigned a unique, de-identified alphanumeric code, encompassing the research center code, enrollment order, and randomization group identifier, ensuring data traceability. A designated research coordinator will maintain sealed, sequentially numbered opaque envelopes containing randomization assignments. Immediately before entering the operating room, a blinded circulating nurse will open the envelope to determine group assignment. Following verification of the group allocation details, the envelopes will be resealed, and this procedure will be conducted without disclosing the information to the patients. To ensure blinding, we will informed patients during preoperative consultation about potential sensory experiences during treatment, including sensations of pricking, needle-like stimulation, warmth, and vibration. We will explicitly emphasize that individual perception of stimuli varies significantly and that sensation intensity should not be used to assess treatment efficacy. Moreover, all stimulation devices will be designed with uniform appearance, with differences limited to electrical output parameters, thereby further preserving the integrity of the blinding procedure. The device will be preset to patient-specific maximum tolerable parameters by independent researchers not involved in the research, and will remain in a black screen state upon entering the operating room. All individuals involved in outcome assessment, data analysis, surgical procedures, and study participants remained blinded to group allocation. With regard to the initial administration of stimulation during hepatic portal occlusion, standard practice at this institution involves the surgeon informing the anesthesiologist and circulating nurse about surgical progress at this stage. However, these personnel were not provided with details regarding the specific stimulation protocol, thereby ensuring the maintenance of blinding within the surgical team throughout the procedure. Prior to study commencement, outcome assessors will accept rigorous blinding training, familiarizing themselves with assessment procedures and standards to minimize subjective influences on results.

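### The amplitude calibration rule in 2.9 stops for a rise in heart rate but not for a fall, although 2.7 names bradycardia as a possible harm (minor safety point)

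*Protocol article*

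**What the plan says.** Section 2.9 (Study interventions) of the protocol article sets out how the active amplitude is found. It starts at 0, "incrementally increasing by 1 based on patient response". Four events end the increase: reported discomfort, a pained face, or, in the article's words, "when stimulation causes oxygen saturation to drop below 95% or heart rate to increase by more than 20" per cent, which supplies the saturation and heart-rate triggers. The amplitude then goes to just under the level that caused the event and is "maintained at a constant stimulus intensity output for 60 min".

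Section 2.9 also says when this is done for session 1: "The collection of the intensity of the first intervention will be conducted on the day before the surgery", after consent. Section 2.6 describes the target: "The device will be preset to patient-specific maximum tolerable parameters by independent researchers not involved in the research".

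Section 2.7 (Unblinding) lists the possible harms: "ear dermatitis, local bleeding at the stimulation site, ear pain, bradycardia, and cardiac arrhythmias". It adds that, in the intervention phase, "participants will undergo systematic evaluation to identify potential complications associated with taVNS and life-threatening symptoms", and that unblinding follows if such a complication occurs.

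**The concern.** The article gives a numerical heart-rate limit for setting the dose, but in one direction only. The one harm in 2.7 that has a rate direction, bradycardia, points the other way. Cardiac arrhythmias, also listed there, may include fast rhythms, but they supply no lower limit.

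The person calibrating the device is therefore told when a rise should end the increase and is told nothing about a fall. If the heart slows without discomfort, a pained face or desaturation, the rule as written lets the amplitude go on rising. The setting reached is then used from the first portal occlusion in session 1. What is at stake is patient safety in choosing the dose. The primary comparison is not affected.

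**Working it through.** The article states no figure on this point, so there is nothing to reproduce. The check sets the sections side by side and adds a short illustration.

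**Triggers in 2.9 that end the amplitude increase**

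| Trigger | Concerns heart rate? | Covers a fall in heart rate? |
|---|---|---|
| Reported discomfort | No | No |
| Pained face | No | No |
| Saturation below 95% | No | No |
| Heart-rate rise above 20% | Yes | No |

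Of four triggers, one concerns heart rate and none concerns a fall.

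**Does another section supply a lower limit for calibration?**

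- 2.7: evaluation and unblinding, worded for the intervention phase. No heart-rate value.
- 2.9, monitoring of "responses to ensure no adverse reactions": worded for the intervention. No heart-rate value. The explicit termination rule that follows depends on the participant reporting intolerable discomfort.
- 2.11: the device can be stopped during the intervention if a reaction is suspected. No heart-rate value.
- 2.8: ECG, arterial line and, where needed, vasoactive drugs to keep heart rate normal. This applies in theatre, whereas the session 1 intensity is found the day before.
- Table 1: adverse events are recorded from the day before surgery. Recording does not set the amplitude.

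No section gives a lower heart-rate limit for calibration.

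**Illustration.** The documents give no resting rates, so 60, 70 and 80/min are assumed. The absolute limit of 50/min is also an assumption, used only as an example.

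- Present limit: 1.2 × resting rate.
- Same percentage applied downward: 0.8 × resting rate.
- Fall needed to reach 50/min: 1 − 50 / resting rate.

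| Resting rate (/min) | Present rule acts above | Present rule acts below | A 20% fall would act below | Fall needed to reach 50/min |
|---|---|---|---|---|
| 60 | 72 | no limit | 48 | 1 − 50/60 = 16.7% |
| 70 | 84 | no limit | 56 | 1 − 50/70 = 28.6% |
| 80 | 96 | no limit | 64 | 1 − 50/80 = 37.5% |

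At 60/min the absolute limit would act slightly sooner than the relative one (50 against 48/min). At 80/min it would act later, by 64 − 50 = 14/min. The two forms are not interchangeable, and the choice between them is clinical.

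**The case against.** The strongest reply is that 2.9 is a tolerance rule. Discomfort, a pained face and a faster heart are all signs of pain, and 2.6 describes the result as the tolerable maximum. Pain speeds the heart, so on that reading an upward limit is all that is needed. This is partly right, and the upward limit should stay. But the saturation trigger is a physiological safety limit, not a sign of pain. The list already mixes tolerance with safety, and it leaves out the rate harm that the protocol itself names.

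A second reply is that an article may leave device limits to the full protocol, and that raising the amplitude according to patient response lets the operator stop. Discretion does exist. However, the article does not leave the criteria elsewhere: it states them, with a number, in one direction. Following that rule exactly gives the result described.

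A third reply is that no harm is shown. That stands. The taVNS safety review cited in the Discussion does not list bradycardia among the frequencies given there, and the Discussion ties bradycardia to implanted stimulation. Section 2.4 excludes patients with a pacemaker, recent infarction or NYHA class 2 or above. This keeps the point minor.

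A reader might go further and infer that bradycardia during stimulation under anaesthesia would go unanswered, and ask for an in-session heart-rate cut-off. The documents do not support this. In sessions, 2.7 provides evaluation and unblinding, 2.9 close monitoring, and 2.11 discontinuation of the device. In theatre, 2.8 adds ECG, an arterial line and vasoactive drugs to keep heart rate normal. A fixed in-session cut-off also has a real cost. Heart rate can fall under remifentanil, propofol and sevoflurane for reasons unrelated to stimulation, and because sham delivers no current, each such cut would remove real dose from the active arm alone.

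**Conclusion.** The point holds for calibration only. The rule in 2.9 limits a heart-rate rise and has no trigger for a fall, although 2.7 names bradycardia as a possible harm. As written, a fall without symptoms or desaturation does not stop escalation.

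This is a cheap patient-safety improvement of minor weight. It does not alter the test, the sample size or the ALT analysis, and it is no reason to doubt the trial's result. How often such a fall occurs, and how many a lower limit would catch, cannot be estimated from the documents. The table above shows only where the rule acts, at assumed resting rates. The conclusion rests on the published article; a lower limit in an operating procedure not shown here would settle it.

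**What to change.** In 2.9, change the heart-rate trigger at calibration to a change of more than 20% in either direction from the rate just before stimulation. Alternatively, keep the upward limit and add an absolute lower limit chosen by the investigators. The step-back to just below the triggering level stays as it is. No in-session cut-off is proposed.

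The cost is small. The rule already needs a heart-rate reading at calibration, so no new measurement is required. Recruitment is in progress (2.1), so an ethics amendment is needed, and patients calibrated under the present rule should be identifiable. The downside is a somewhat lower amplitude in active-arm patients whose heart slows at calibration. Its size is unknown. A low absolute limit would reduce that loss at higher resting rates, but it would allow a larger fall before acting.

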**Figure 2 fig2:**
[figure not shown]
The stimulation electrode will be placed in the left ear position. taVNS, Transcutaneous auricular vagus nerve stimulation.

### Outcomes

2.10

#### Primary outcome

2.10.1

The primary endpoint is serum alanine aminotransferase (ALT) levels on postoperative day 2. Perioperative hepatic injury occurs in two distinct phases. The first phase, occurring 2–6 h after reperfusion, is characterized by Kupffer cell-induced oxidative stress and the initiation of cell necrosis and apoptosis. The second phase, spanning 6–48 h after reperfusion, involves inflammatory cell aggregation in the hepatic microvascular system, including sinusoids and post-sinusoidal regions, accompanied by sinusoidal congestion, neutrophil adhesion leading to blood flow obstruction, and inflammatory cell extravasation into the hepatic parenchyma (31, 32). Furthermore, evidence indicates that intermittent stimulation effectively alleviates patient discomfort and improves treatment safety (33). Based on these pathological mechanisms, we implemented taVNS intervention throughout the entire hepatic injury inflammatory response to maximize inflammation mitigation and minimize hepatic damage. Liver injury severity is classified as follows: ① Mild acute liver injury (ALI) is typically defined as 2 × upper limit of normal (ULN) ≤ ALT < 5 ULN; ② Moderate ALI is typically defined as 5 ULN ≤ ALT < 15 ULN; ③ Severe ALI requires: International Normalized Ratio (INR) ≥ 2.0, ALT ≥ 10 ULN, serum total bilirubin (TBiL) ≥ 3.0 mg/dL, and absence of hepatic encephalopathy (34–36). Baseline venous blood samples will be obtained during the preoperative anesthesia visit after obtaining informed consent (t0). The primary endpoint will be venous blood samples collected at 7:00 AM on the second postoperative day (t4) after stimulation cessation.

#### Secondary outcomes

2.10.2

ALT levels, will be measured on the fifth postoperative day (t6).AST, total bile acids (TBA), total bilirubin (TBIL), direct bilirubin (DBIL), creatinine (Cr), and blood urea nitrogen (BUN) levels, will be measured at 7:00 a.m. on the second and fifth postoperative days (t4 and t6).Interleukin-6 (IL-6) and TNF-*α* levels, will be measured at 7:00 a.m. on the second postoperative day (t4).Postoperative recovery quality, will be assessed using the Postoperative Quality of Recovery-15 (QoR-15) scale on the first, second, fifth, and thirtieth postoperative days (t3-t4 and t6-t7). The QoR-15 scale evaluates 15 items across physical adaptability, self-care ability, psychological state, and postoperative pain, with scores ranging from 0 to 10 (total score 150); lower scores indicate poorer postoperative recovery (37).Anxiety levels will be evaluated using the Self-Rating Anxiety Scale (SAS) on the first, second, fifth, and thirtieth postoperative days (t3-t4 and t6-t7). The SAS comprises 20 items scored 1–4, with a raw score range of 20–80. The standard score is calculated by multiplying the raw score by 1.25, yielding a total score of 25–100. Anxiety is defined as a SAS score ≥50, with severity categorized as: 25–49 (no anxiety), 50–59 (mild anxiety), 60–69 (moderate anxiety), and 70–100 (severe anxiety) (38).Pain intensity will be measured using the NRS on the first, second, fifth, and thirtieth postoperative days (t3-t4 and t6-t7), ranging from 0 (no pain) to 10 (most severe pain imaginable) (39).The incidence of postoperative delirium will be evaluated using the Confusion assessment method (CAM) scale on the first, second, fifth, and thirtieth postoperative days (t3-t4 and t6-t7) (40).Fatigue levels will be assessed using the Fatigue Severity Scale (FSS) on the first, second, fifth, and thirtieth postoperative days (t3-t4 and t6-t7). The FSS comprises nine statements scored 1–7, with a total score range of 9–63. Higher scores indicate more severe fatigue, with ≥ 36 signifying significant fatigue symptoms (41).Postoperative gastrointestinal function recovery will be evaluated using the Intake-Food Intolerance-Emesis-Dyspepsia-Endoscopy-Duration (I-FEED) scoring system on the first, second, third and fifth postoperative days (t3-t6), Some patients with severe gastrointestinal dysfunction (Postoperative Gastrointestinal Dysfunction, POGD) were followed up until the end of the surgery. I-FEED, recommended by the American Society for Enhanced Recovery and Perioperative Quality, is the primary method for diagnosing POGD. The scoring system classifies gastrointestinal function as follows: 0–2 points indicate normal function; 3–5 points suggest intolerance; ≥ 6 points signify POGD (42).Time to first flatus, defecation, and oral intake will be recorded.

### Data collection and management

2.12

These data will be recorded in a case report form (CRF). Preoperative information includes comprehensive demographic data, medical history, current health status, surgical type, nutritional control status scoring (including preoperative hemoglobin levels and lymphocyte count), CAM, SAS, FRAIL and FSS scores. Additionally, preoperative liver and kidney function indicators, coagulation function parameters and inflammatory markers will be collected. Intraoperative data will encompass detailed metrics such as blood loss, urine output, ischemic occlusion frequency and duration, mean arterial pressure (MAP) and central venous pressure (CVP) during occlusion and reperfusion phases, extent of hepatectomy [Hepatectomy is classified as minor when involving up to four wedge resections or two segmental resections, and major when exceeding these criteria, such as left or right hemihepatectomy (43)], detailed medication records, and surgical and anesthesia duration. Postoperative data will include liver and kidney function, inflammatory markers, NRS for pain intensity, QoR-15 for overall recovery assessment, CAM and FSS scores for delirium and fatigue incidence, and gastrointestinal function recovery data.

After the trial, all participant data will be analyzed by an independent, professionally trained investigator who was not involved in any aspect of the experiment. Personnel responsible for perioperative follow-up and blood sample collection were blinded to group allocation and will not participate in interventions. Following sample collection, specimens will be centrifuged, classified, and recorded in an encrypted Excel spreadsheet stored on an iPad. Test results will be subsequently entered into the same Excel file. An independent investigator collected pre-, intra-, and post-operative questionnaire data, initially recording them on paper case report forms, then transcribing them into a Word document on the iPad. In accordance with national regulatory requirements, original samples will be stored in a dedicated anesthesia freezer pending authorized access. The iPad containing follow-up information, case report forms, and other sensitive data will be password-encrypted and secured in a locked cabinet, accessible only to authorized personnel for data entry, processing, and analysis.

